### 4.3 Study Procedure

Table 1. Study Visits

| Event of Assessment                                                                                | Visit 1(Screening Visit) | Visit 2(Assessment after ApneaLink™ –home sleep test) |
|----------------------------------------------------------------------------------------------------|--------------------------|-------------------------------------------------------|
| Eligibility Screen                                                                                 | X                        |                                                       |
| STOP-Bang questionnaire                                                                            | X                        |                                                       |
| Visual Analog Scale for pain                                                                       | X                        |                                                       |
| Enrollment & ApneaLink Sleep Breathing, Bittium Faros™ 180 and Caretaker™ Medical cNIBP Monitoring | X                        |                                                       |
| Demographics                                                                                       | X                        |                                                       |
| History of Injury                                                                                  | X                        |                                                       |
| General Health History                                                                             | X                        |                                                       |
| Laboratory blood tests (CRP and CBC)                                                               |                          | X                                                     |
| Participants' experience on the use of a home-based sleep test                                     |                          | X                                                     |
| Modified Ashworth Scale                                                                            | X                        |                                                       |

Untreated sleep-related breathing disorders as an aggravating factor for neuropathic pain, cardiovascular dysfunction and spasticity following spinal cord injury

Visit 1 and 2 will each last approximately an hour.

Those individuals with clinical warning signs for SRBDs will undergo a home-based sleep study using the ApneaLink™ (Picture 1) device to confirm the diagnosis of SRBD (n=30). Based on the results of the home-based sleep study, individuals with SRBD will be grouped into mild (n=10), moderate (n=10) and severe sleep apnea (n=10). Also, individuals without clinical warning signs for SRBD will undergo a home-based sleep study using ApneaLink™ in order to identify 10 study participants without SRBDs (“control cases”).

All participants will also undergo cardiovascular evaluation during sleep using the Bittium Faros™ 180 (Picture 3) and Caretaker™ Medical cNIBP monitor (Picture 2) devices to assess sympathetic activity during sleep in all study participants (n=40). All participants will be examined with regards to their degree of spasticity as assessed using the Modified Ashworth Scale. Also, all participants will undergo laboratory blood tests to measure their serum CRP level.

Furthermore, an economic analysis will be undertaken in order to compare the costs of the home-based sleep study with the conventional polysomnography in a sleep clinic. For this purpose, the costs of the home-based sleep test will be estimated based on our experience during this study. The costs of the conventional polysomnography will be obtained from the sleep clinic at Sunnybrook Hospital where [name], co-investigator in this study, works. The professional and technical fees will be derived from the Ontario Health Insurance Plan (OHIP) – Schedule of Benefits, Physician Services.

All participants who are diagnosed with moderate-to-severe SRBDs during the study will be referred to [name] or other sleep specialist for consultation and CPAP therapy. Also, study participants whose CRP levels are greater than 10 mg/L (normal range up to 3 mg/L) will be immediately referred to their family physician (or emergency if symptoms or signs of systemic infection) for further investigations and treatment because a CRP greater than 10 mg/L is suggestive of infection or primary inflammatory disease.

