## **2.0 Background and Rationale**

### **2.1. Summary of previous findings**

The majority of individuals living with SCI experience chronic pain, including nociceptive and neuropathic pain. Nociceptive pain is caused by activation of the normal peripheral terminals of primary sensory neurons (“nociceptors”) that detect signs of actual or incipient tissue injury such as inflammation. Neuropathic pain is caused by injury or disease of the nervous system. SCI-induced neuropathic pain is considered a pathological, maladaptive consequence of damage to, and inflammation of, the central nervous system. Neuropathic pain occurs in 48% to 92% for individuals with SCI. Given that neuropathic pain is a frequent and usually permanent complication that is typically resistant to treatment, there is a great need for more effective approaches to manage SCI-induced neuropathic pain.

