## **3.0 Study Objectives and Hypothesis**

### **3.1 Primary study objectives:**

- (1) To evaluate the potential association of neuropathic pain with SRBDs in individuals with SCI;
- (2) To study the potential relationship between cardiovascular autonomic dysfunction and SRBDs in individuals living with SCI;
- (3) To evaluate the potential association of spasticity with SRBDs after SCI.

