### **3.3 Study Hypothesis**

- (a) Individuals with SCI and untreated SRBDs more frequently develop more severe neuropathic pain;
- (b) Individuals with SCI and untreated SRBDs develop more significant cardiovascular dysfunction (i.e., reduced heart rate variation, more frequent episodes of autonomic dysreflexia during sleep);
- (c) Individuals with SCI and untreated SRBDs more frequently develop more severe spasticity.

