#### **4.1.1 Primary Outcome measures:**

- a) The presence and intensity of neuropathic pain as assessed using the Visual Analog Scale (VAS; range: 0 to 100) and daily amount of analgesics (pregabalin, neurontin, opioids, etc.);

Untreated sleep-related breathing disorders as an aggravating factor for neuropathic pain, cardiovascular dysfunction and spasticity following spinal cord injury

- b) The cardiovascular activity during sleep based on the peripheral arterial tone and overall heart rate variability as recorded using the Bittium Faros™ 180 device and Caretaker™ Medical cNIBP monitor device;
- c) The number of episodes of autonomic dysreflexia during sleep and their association with apneas and hypopneas by combining the recorded data from the ApneaLink™, Bittium Faros™ 180 device and Caretaker™ Medical cNIBP monitor devices;
- d) The degree of spasticity in the upper and lower limbs as assessed using the Modified Ashworth Scale;
- e) Serum CRP level.

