## **5.2 Exclusion criteria:**

- Patients with a non-traumatic spinal cord disease at risk for disease recurrence during the study (*e.g.*, demyelinating spine diseases such as neuromyelitis optica and multiple sclerosis, spinal cord malignancy); of note, patients with other causes of non-traumatic spinal cord disease are eligible for this study.
- Concomitant significant diseases of the central nervous system causing neurological deficits (*e.g.*, concomitant traumatic brain injury, stroke, dementia, Parkinsonism, multiple sclerosis)
- Preinjury chronic pain (*e.g.*, fibromyalgia)
- Psychiatric disorders that could affect the home-based sleep study using the ApneaLink™ and cardiovascular evaluations.
- Neuromuscular diseases (*e.g.*, myasthenia gravis)
- Current substance misuse
- History of primary hypersomnia (*e.g.*, narcolepsy, idiopathic hypersomnia). Of note, hypersomnia is defined as prolonged sleep periods (*i.e.*, more than 10 hours per night).

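### Presence of neuropathic pain, half of the first primary outcome, is assigned to a pain VAS and an analgesic amount, neither of which can show that pain is neuropathic

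*Protocol*

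**What the plan says.** The target is neuropathic pain throughout. Section 3.1 gives the first primary objective as "To evaluate the potential association of neuropathic pain with SRBDs in individuals with SCI". Hypothesis (a) in Section 3.3 covers both frequency and severity: "Individuals with SCI and untreated SRBDs more frequently develop more severe neuropathic pain". Primary outcome (a) in Section 4.1.1 is "The presence and intensity of neuropathic pain as assessed using the Visual Analog Scale (VAS; range: 0 to 100) and daily amount of analgesics", with pregabalin, neurontin and opioids given as examples of the analgesics.

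Elsewhere the qualifier is lost. The pain row of the visit schedule (Section 4.3, Table 1) reads "Visual Analog Scale for pain". The sample size in Section 7 treats pain on the VAS as the primary outcome, again without the word neuropathic.

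On the population, Section 2.1 states "The majority of individuals living with SCI experience chronic pain, including nociceptive and neuropathic pain", describes the two as having different causes, and adds "Neuropathic pain occurs in 48% to 92% for individuals with SCI". Section 5.1 does not require neuropathic pain at entry. The only pain-related exclusion in Section 5.2 is "Preinjury chronic pain".

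**The concern.** A VAS says how much pain there is, not what kind. If nothing else in the study settles the kind, then presence of neuropathic pain has no operational definition, and the frequency part of hypothesis (a) has no matching measurement. The intensity part may also mix in post-injury nociceptive pain, which the hypothesis does not concern.

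The error could go either way. Nociceptive pain unrelated to SRBDs can hide a real difference in how often neuropathic pain occurs. Nociceptive pain that is related to SRBDs would have its association credited to neuropathic pain. This is a matter of data collection, so it cannot be left to a statistical analysis plan: pain type not recorded at the visit cannot be reliably recovered by analysis.

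**Working it through.** **Step 1. Can any stated measure identify pain type?**

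| Place in the Protocol | What it supplies | Identifies neuropathic pain? |
|---|---|---|
| 4.1.1(a), VAS | intensity, 0 to 100 | No |
| 4.1.1(a), daily analgesics | amount of drugs, opioids included | No: opioids are not specific to neuropathic pain, and taking a drug does not classify the pain |
| 4.2, item (2) | medicines for neuropathic pain and/or spasticity, collected as potential confounders | No |
| 4.3, Table 1 | a VAS for pain, Visit 1 | No |
| 5.1 and 5.2 | no entry requirement; pre-injury chronic pain excluded | No: post-injury nociceptive pain can enter |
| 7 | pain on the VAS | No |

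No criteria, questionnaire, examination or classification step for pain type appears in the text at hand.

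**Step 2. How many participants could be affected?** Input: neuropathic pain in 48% to 92% (Section 2.1). The complement is 100 - 92 = 8% to 100 - 48 = 52%. If the study sample resembles that population, this share has no neuropathic pain but may still score above zero.

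**Step 3. The Protocol's own figure.** Section 7 gives 10 per group for 25 mm, 90% power and two-sided 5%, with no SD. Solving n = 2·SD²·(1.960 + 1.282)²/25² for n = 10 gives SD = 25/(3.242 × √0.2) = 17.2 mm; with the t-test it is 16.3 mm. The figure can be met with such an SD, and this point does not contest it.

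**Step 4. What does an unclassified score do to the presence component?** Let p0 and p1 be the proportions with neuropathic pain in two groups, μN its mean VAS, and μO the mean VAS of other pain in people without it. Take μN and μO as equal in both groups.

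- Unclassified VAS difference: (p1 - p0)(μN - μO)
- Classified difference, 0 if no neuropathic pain: (p1 - p0)μN

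Take p0 = 0.48 and p1 = 0.92, the two ends of the Protocol's range used as an assumed contrast, so p1 - p0 = 0.44. Take μO = 40 mm (assumption).

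| μN (assumption) | Unclassified | Classified |
|---|---|---|
| 30 mm | 0.44 × (30 - 40) = -4.4 mm | 0.44 × 30 = 13.2 mm |
| 40 mm | 0.44 × 0 = 0 mm | 0.44 × 40 = 17.6 mm |
| 55 mm | 0.44 × 15 = 6.6 mm | 0.44 × 55 = 24.2 mm |

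If people without neuropathic pain have no other pain (μO = 0), the two columns agree and nothing is lost. The size of the loss depends on μO, which the Protocol does not give.

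**The case against.** Several points on the other side are fair.

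- Section 4.1.1 names neuropathic pain as the construct: "The presence and intensity of neuropathic pain as assessed using the Visual Analog Scale". The unqualified label is a short row in a schedule, and that schedule is not exhaustive, since it has no row for analgesic amounts either. An assessor may ask about neuropathic pain only. Pain type may also be noted in the Visit 1 history or in the chart review of Section 10.2. This stands as a possibility, but the Protocol does not say that any of it happens.
- The VAS is not the sole measure, because the analgesic amount is part of the outcome. This stands as a description, but does not close the gap, for the reason in Step 1.
- Section 2.1 lists both pain types as occurring in the population. A reader might infer that most individuals have both; the sentence does not say so.

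A reader might also infer a definite loss of power. If 30% of participants had only unrelated pain, a 25 mm difference would become 0.7 × 25 = 17.5 mm, and power with 10 per group at SD 16.3 mm would fall from 90% to 62% (83% to 37% for shares of 10% to 50%). The arithmetic is right, but it does not measure this defect. The share is assumed and the SD is solved backwards. Moreover, classifying pain and scoring those participants 0 leaves the mean difference at 0.7 × 25 = 17.5 mm and widens the spread. With neuropathic pain at 55 mm, the between-type variance is 0.7 × 0.3 × 55² = 635 mm², against 0.7 × 0.3 × (55 - 40)² = 47 mm² when other pain scores 40 mm. In simulation (neuropathic means 30 and 55 mm, other pain 40 mm), power was about 57% unclassified and about 32% with zeros. The remedy would not recover that power.

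**Conclusion.** The point holds as one of validity. As written, the stated measures cannot establish the presence of neuropathic pain, and objective 1 may be answered for pain of any type. It would go too far to say that objective 1 will be answered for any pain, or that nociceptive pain will be scored as neuropathic: Section 4.1.1 names the intended construct, and practice at the visit is not described.

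On the Protocol's prevalence range, 8% to 52% of participants could lack neuropathic pain, provided the sample resembles the population cited. The clearest consequence is for the frequency hypothesis. Under the assumptions in Step 4, a shift in presence from 48% to 92% leaves -4.4 to 6.6 mm on an unclassified VAS, against 13.2 to 24.2 mm when classified. That contrast is deliberately wide and shows the mechanism; it is not a forecast. No claim about lost power for the 25 mm comparison is made. The change should be made because it is inexpensive and concerns the outcome on which the study is sized.

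**What to change.** 1. At Visit 1, record for each participant whether neuropathic pain is present, either by the examining clinician's classification or with a short validated neuropathic-pain questionnaire. Name the method in Section 4.1.1 and add a row to Table 1.
2. State in Section 4.1.1, Table 1 and Section 7 that the VAS rates neuropathic pain, so that the three places agree.
3. Compare presence (yes/no) across the four groups with the Fisher exact test already planned for categorical variables. Analyse neuropathic-pain intensity separately, and say whether participants without it are left out or scored 0, since zeros widen the spread.

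The cost is a few minutes at Visit 1, extra CRF fields, and chart-based classification for participants already assessed, which will be less reliable than classification at the visit.

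The presence comparison will be imprecise at the minimum group size. For two groups of 10 with 5 and 9 affected (48% and 92% rounded), the two-sided Fisher p-value is 2 × (252 × 10 + 210)/38,760 = 0.14. Presence should therefore be reported with confidence intervals.

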### **Sample Size**

N= 70 participants

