### **Study Duration**

May 1st 2019 to March 30th 2024 (36 months)

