#### **4.2 Description of the type/design of the study**

This is 3-year cross-sectional, prospective study.

- (1) Individuals with SCI frequently decline to stay overnight to complete formal polysomnography due to their concerns about availability of proper support, funding for attendants and the accessibility of the sleep disorder clinics. Given this, we decided to use a home-based or hospital-unattended sleep test (ResMed ApneaLink Air™) that is a practical, less costly, validated and reliable surrogate for diagnosis of the SRBDs. A trained research assistant from Sunnybrook Health Science Centre with expertise on the setting up and use of ResMed ApneaLink™, Bittium Faros™ 180 and Caretaker™ Medical cNIBP monitor devices will be available to assist the participants who have questions or problems with setting up the sleep apnea testing. The process for the technical support for the home based-sleep study will include the following steps:
  - (a) The research assistant from Sunnybrook Health Science Centre will receive a notification by phone from the research coordinator from Lyndhurst stating that a new participant will undergo home-based sleep studies. The study participant identifying number (i.e. “study participant ID #...”) along with their address and minimal clinical information (only level and severity of spinal cord injury) will be provided.
  - (b) The study participant will receive the name and phone number of the research assistant from Sunnybrook Health Science Centre and will be instructed to call them if there are any questions or concerns only during home-based sleep study (12 hours overnight support).
  - (c) If the study participant is unable to set up the home-based sleep study devices, they will be offered to receive a visit from the research assistant at their residence. If the study participant agrees, the research assistant will provide technical support at their residence.

Untreated sleep-related breathing disorders as an aggravating factor for neuropathic pain, cardiovascular dysfunction and spasticity following spinal cord injury

If the study participant disagrees and the setting up is not possible, the study participant will be withdrawn from the study.

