#### **4.4 Number of Participants**

Seventy individuals will be invited to take part in this study.

Based on the results of the home-based sleep study, individuals with SRBD will be grouped into mild (minimum of 10), moderate (minimum of 10) and severe sleep apnea (minimum of 10).

Individuals without clinical warning signs for SRBD (minimum of 10) will undergo a home-based sleep study using ApneaLink™ in order to identify 10 study participants without SRBDs (“control cases”).

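### The protocol counts 70 participants in one place and 40 in another, with groups of ten as fixed sizes and as minimums; these must be reconciled, as must the study duration.

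*Protocol*

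**What the plan says.** **Total.** The Protocol Summary (Sample Size) reads "N= 70 participants". Section 4.4 reads "Seventy individuals will be invited to take part in this study". Section 4.3 describes cardiovascular monitoring "to assess sympathetic activity during sleep in all study participants (n=40".

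**Group sizes.** In Section 4.3, people with clinical warning signs are tested with the "device to confirm the diagnosis of SRBD (n=30", and those with SRBD are then "grouped into mild (n=10), moderate (n=10) and severe sleep apnea (n=10"; people without warning signs are tested to find 10 controls. Section 4.4 has the SRBD participants "grouped into mild (minimum of 10), moderate (minimum of 10) and severe sleep apnea (minimum of 10". It also has at least 10 people without warning signs tested, again to find 10 controls.

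**Requirement.** Section 7 asks for 10 per group across four groups, to detect 25 mm on the pain VAS with 90% power at a two-sided 5% level.

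**Duration.** The Protocol Summary (Study Duration) runs from 1 May 2019 to 30 March "2024 (36 months". Its Accrual Period entry is five years. Section 4.2 states "This is 3-year cross-sectional, prospective study".

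**The concern.** Both 70 and 40 are attached to the study's participants, and no text says that one counts people invited and the other people tested or analysed. Reading 70 as invitations only does not work, because the Summary calls the 70 participants. A group of n=10 and a group of at least ten are also different statements about when a group is full.

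This matters because group membership follows from the sleep test result, so group sizes cannot be set at enrolment. A team working from Section 4.3 could regard the study as complete at 40. A team working from the Summary and Section 4.4 would go on to 70. No rule says when recruitment ends or what happens if a severity group does not fill. VAS pain is recorded at Visit 1 (Table 1), so pain scores could be known when that choice is made.

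**Working it through.** **1. Where 40 comes from.** Four groups × 10 (Section 7) = 40, and 30 SRBD + 10 controls (Section 4.3) = 40. So 40 is the per-group requirement multiplied out, with no allowance for an uneven split. The gap to the Summary is 70 − 40 = 30 participants.

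**2. If 40 were the number tested.** Every group reaches 10 only if the split is exactly 10/10/10/10.

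- One pool, with each group equally common (the most favourable shares): 40!/(10!)⁴ × (1/4)⁴⁰ = 0.0039, or 0.4%.
- Two streams as in Section 4.3, with ideal screening: all 30 flagged people have SRBD, each severity is equally likely among them, and all 10 unflagged people are negative. Then 30!/(10!)³ × (1/3)³⁰ = 0.027, or 2.7%.

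**3. If 70 were the number tested.** This is the exact multinomial probability that all four groups reach at least 10. The protocol gives no severity split, so the shares are assumptions, listed as the four groups' shares of everyone tested.

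| Assumed split | P(all four ≥ 10), 70 tested | P(at least one < 10) | Number tested for a 90% chance |
|---|---|---|---|
| 25/25/25/25 | 96% | 4% | 65 |
| 30/30/20/20 | 83% | 17% | 75 |
| 40/30/15/15 | 36% | 64% | 102 |

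So 70 is a workable total if the groups are roughly balanced, but it does not guarantee the minimums.

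**4. Duration.** 1 May 2019 to 1 May 2023 is 48 months. To 1 March 2024 it is 58, and to 30 March 2024 about 59. The bracketed 36 months and the three-year description agree with each other but not with the dates. The five-year accrual (60 months) is close to the dates but not to the 36 months.

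**The case against.** The strongest reply is that Section 4.3 never caps testing at 40. People without warning signs are tested in order to find ten controls, so 40 can be read as the number classified into groups and analysed, with 70 approached to secure them. The minimums in Section 4.4 fit that reading. Section 4.3 may simply not have been updated; the protocol is at Version 7. This is plausible, but it is inference: the protocol does not say it, and the Summary's wording does not fit it.

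Several stronger readings are tempting and are not supported:

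- A reader might infer that 40 tested people cannot give ten per group. They can; it is only very unlikely.
- A reader might infer that the recruitment target is undefined. Seventy is stated twice, once in the section on participant numbers. The target is stated inconsistently.
- A reader might infer that precision is undefined. Section 7 fixes the per-group size, difference, power and significance level, and these do not change between 40 and 70. It states no VAS standard deviation, but that is a separate matter. It also means that a comparison of power between 40 and 70 would rest on an assumed value.
- A reader might infer that some participants would miss cardiovascular monitoring or the CRP test. Section 4.3 gives both to all participants under either total; only the count in brackets conflicts.

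**Conclusion.** The concern holds as an unreconciled contradiction within the current protocol: 70 against 40 participants, and fixed against minimum group sizes. Thirty participants depend on which text is followed. Read as the number tested, 40 would almost never fill the four groups (0.4% to 2.7% under favourable assumptions). Seventy would fill them with a chance between about 96% and 36% over the three splits tried.

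These probabilities rest on assumed shares. The figures for 70 also treat those tested as one pool; recruiting by warning signs could help to fill the control group, but it does not fix how severity falls among people with SRBD.

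The duration mismatch, 59 months by the dates against 36 as stated, is a separate error and needs no assumption. Both should be corrected. Neither shows that the study lacks a target.

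**What to change.** - Use 70 enrolled as the single total in the Summary, Section 4.3 and Section 4.4.
- In Section 4.3, replace n=30, n=40 and the n=10 group sizes with the minimum-of-ten wording of Section 4.4.
- State separately the numbers invited, tested and analysed.
- Fix in advance that recruitment ends at the stated total, whatever the outcome data show.
- State that if a group ends below ten, the per-group size and 90% power in Section 7 are not met for comparisons with that group. Keep the minimum of ten; accepting groups at whatever size they reach would abandon Sections 4.4 and 7.
- Reconcile the Study Duration dates and their 36 months, the three-year description in Section 4.2 and the five-year Accrual Period.

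The cost is an editorial amendment, submitted to the REB under Section 10.4. Enrolling 70 is not the same as inviting 70: some people will decline, so more than 70 may have to be approached. Fewer than 70 may complete the sleep test, because Section 4.2 withdraws a participant who declines a home visit when the devices cannot be set up, and Section 5.3 allows withdrawal at any time.
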